**Pilot study success criteria**

***1.Recruitment:*** The overall target recruitment for the pilot study is at least 100 residents across the participating CHs. Number of CHs and recruitment rates will be monitored during the internal pilot and the following outcomes applied:

**Green:** recruitment of >90 residents. *Continue* as possible to recruit to time and target.

**Amber:** recruitment of 76-90 residents. *Continue but modify protocol*as may be possible to recruit to time and target with implementation of contingency plans (e.g. increased number of sites)**.**

**Red:** recruitment ≤75 residents or less.*Discuss discontinuation with TSC, DMEC, sponsor and funders.* We will review recruitment in each site on a monthly basis, both in the internal pilot and the main trial, to enable us to identify and address any issues as they arise.

***2. Adherence to stimulation:*** The target is for all residents to receive a minimum of two thirds of the electrical stimulation programme, which is at least 8 of the 12 sessions. These will be monitored by the stimulation diaries recorded by the administering CH staff as well as the data recorded by the electrical stimulators. The following outcomes will apply:

**Green:** >70% residents receive >8 stimulation sessions. *Continue without modification*.

**Amber:** 50-70% residents receive >8 stimulation sessions. *Continue but modify protocol.* (eg adjust timing and location of delivery to suit resident’s situation)

**Red:** <50% residents receive >8 stimulation sessions. *Discuss discontinuation* with *TSC,DMEC, sponsor and funders*.

***3. Completeness of 24hour pad weigh test (PWT):*** The target is a complete PWT at 6-weeks post-randomisation, for all participating residents. The following progression outcomes will apply

**Green:** >70% residents with complete 6-week PWT (no missing data). *Continue without modification*.

**Amber:** 50-70% residents with complete 6-week PWT. *Continue but modify protocol.* Implement contingency measures as planned (eg Repeat any incomplete PWTs; provide further staff education).

**Red:** <50% residents with complete 6-week PWT. *Discuss discontinuation with TSC, DMEC, sponsor and funders.*

***4. Fidelity to the allocated intervention (TPTNS or sham):*** The target is for all participating residents to receive the intervention protocol (duration and intensity of stimulation and correct ankle position) associated with the group to which they were allocated.

**Green:** >70% residents correctly receive >8 stimulation sessions. *Continue without modification*.

**Amber:** 50-70% residents correctly receive >8 stimulation sessions. *Continue but modify protocol.* Implement contingency measures as planned (eg alert CH staff to identified deficits and provide further education and support).

**Red:** <50% residents correctly receive >8 stimulation sessions. *Discuss discontinuation with TSC, DMEC, sponsor and funders.*

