The allocated treatment (TPTNS or sham) will be offered to the resident a maximum of two times in any 24-hour period. If refused when first offered (verbally or by non-verbal behaviour) the treatment will be postponed for at least an hour and then offered one further time. Records of acceptance and refusals are documented in the resident’s treatment diary. Adherence to the TPTNS or sham stimulation programme is one of the progression criteria to full scale trial from the internal pilot. While aiming to complete a full 12-session programme over the 6-week intervention period contingency measures will be implemented if four or more sessions are refused by the resident or missed. Such measures will include approaching the resident at a later time (a maximum of two requests in any 24-hour period), different place or different day.

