10.3 Process evaluation data analysis

Process evaluation data analysis will address the adherence to the stimulation programme by group, at time point 1 (6-weeks post-randomisation), the end of the stimulation programme. Characteristics of residents, and the stimulation programme they received will be described using appropriate summary measures and the proportion who received the therapeutic minimum > 8 stimulation sessions and the full 12 session programme presented. Overall fidelity to the allocated group will also be assessed and presented to illuminate resident elements of the outcome analysis including: total stimulation time, mean intensity of stimulation and accuracy of electrode position. Stimulation diaries will be analysed to identify data to inform our understanding of when, how and who delivers the electrical stimulation in practice.

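### Pilot adherence criterion: the target is at least 8 of 12 sessions, but the traffic-light bands count more than 8, so residents with exactly 8 meet the target and are not counted

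*Protocol*

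**What the plan says.** Protocol Section 3.4, criterion 2 (adherence), sets as its target that all residents receive "a minimum of two thirds of the electrical stimulation programme, which is at least 8 of the 12 sessions". The three bands printed directly below it use a different operator:

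- green: ">70% residents receive >8 stimulation sessions"
- amber: "50-70% residents receive >8 stimulation sessions"
- red: "<50% residents receive >8 stimulation sessions"

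Criterion 4 (fidelity) uses the same session cut in all three of its bands; green, for example, is ">70% residents correctly receive >8 stimulation sessions". Section 10.3 plans to report "the proportion who received the therapeutic minimum > 8 stimulation sessions".

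Under the continuation decision in Section 3.4, the trial goes on if every criterion is green or amber, with amber requiring workable modifications. Red leads to a discussion of discontinuation with the TSC, DMEC, funder and sponsor; the opening of Section 3.4 describes red as a pause. Section 3.4 also says that the TSC will review and finalise the criteria.

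**The concern.** The target and the rule meant to implement it do not count the same residents. Someone with exactly 8 sessions has met the target in words but falls outside the count in criterion 2. The same resident is left out of criterion 4 and of the Section 10.3 proportion, which attaches a strict inequality to something it calls a minimum.

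Two of the four progression criteria depend on this cut. If the pilot data arrive while both versions stand, the operator could be settled after the results are known, and that choice alone could decide the colour of a band. A progression rule fixed in advance is meant to prevent that.

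**Working it through.** **The plan's own figure.** Two thirds of the programme: 12 × 2/3 = 8 exactly. The target sentence is therefore arithmetically consistent. The printed bands require 9 or more: 9/12 = 75%.

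**Inputs from the protocol.** 12 sessions (Section 3.1); green above 70%, amber 50-70%, red below 50% (Section 3.4); pilot of 100-140 residents (Section 3). In a pilot of 100, green needs 71 residents and red means fewer than 50; in a pilot of 140, 99 and fewer than 70.

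**Input not in the protocol.** The distribution of sessions received per resident. I assume a mean uptake per session, p, of 0.60 to 0.85. Sessions are either independent (binomial) or clustered within resident (beta-binomial, correlation ρ from 0.1 to 0.5).

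**Formulae.**

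- Independent: P(X ≥ 8) = Σ C(12,k) p^k (1−p)^(12−k) for k = 8 to 12. P(X ≥ 9) drops the k = 8 term.
- The two readings differ by exactly the share with 8 sessions: C(12,8) p^8 (1−p)^4, with C(12,8) = 495.
- Clustered: beta-binomial with parameters p(1−ρ)/ρ and (1−p)(1−ρ)/ρ.

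**Worked cases, independent sessions.**

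- p = 0.75: share with exactly 8 = 495 × 0.75^8 × 0.25^4 = 0.1936. P(X ≥ 8) = 0.8424, so P(X ≥ 9) = 0.8424 − 0.1936 = 0.6488.
- p = 0.70: share with exactly 8 = 495 × 0.70^8 × 0.30^4 = 0.2311. P(X ≥ 8) = 0.7237, and P(X ≥ 9) = 0.4925 (from unrounded values).

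**Expected share counted as adherent, at least 8 / more than 8.**

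| Mean uptake | Independent | ρ = 0.1 | ρ = 0.3 | ρ = 0.5 |
|---|---|---|---|---|
| 0.60 | 43.8 / 22.5% (red, red) | 47.4 / 32.5% (red, red) | 51.1 / 42.2% (amber, red) | 53.8 / 48.3% (amber, red) |
| 0.65 | 58.3 / 34.7% (amber, red) | 57.5 / 42.1% (amber, red) | 58.2 / 49.4% (amber, red) | 59.8 / 54.4% (amber, amber) |
| 0.70 | 72.4 / 49.3% (green, red) | 67.4 / 52.6% (amber, amber) | 65.3 / 56.9% (amber, amber) | 65.8 / 60.7% (amber, amber) |
| 0.75 | 84.2 / 64.9% (green, amber) | 76.6 / 63.4% (green, amber) | 72.3 / 64.6% (green, amber) | 71.7 / 67.2% (green, amber) |
| 0.80 | 92.7 / 79.5% (green, green) | 84.7 / 74.0% (green, green) | 79.0 / 72.4% (green, green) | 77.7 / 73.7% (green, green) |
| 0.85 | 97.6 / 90.8% (green, green) | 91.1 / 83.5% (green, green) | 85.2 / 80.0% (green, green) | 83.5 / 80.4% (green, green) |

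The colour can differ for uptake of about 60-75%, usually by one band. The two-band change at 0.70 appears only with fully independent sessions, and there the lower figure misses amber by 0.7 points. The same calculation applies to criterion 4 if p is read as the chance that a session is both received and correctly delivered.

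**The case against.** **The symbol may be an extraction loss.** An underlined greater-than sign, meaning at least, would print bare if underlining was dropped. There is a hint of this: the Appendix 2 flowchart shows a bare less-than sign before 20 for interviews that Section 8.2 caps at 20 inclusive. Calling the cut a minimum in Section 10.3 also fits 8 as the floor. Against it, the red recruitment band in Section 3.4 prints a true less-than-or-equal sign, and the sign before 70% in the same bands must be strict because amber runs to 70%. This remains open and limits confidence in the finding.

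**People stand between the colour and the outcome.** Amber continues with modification, and red opens a discussion rather than stopping the trial. The TSC is to finalise the criteria. All of this stands, and calling the rule a go/no-go gate would overstate it. However, Section 3.4 places the TSC review in June 2018, while the version history dates version 2.0, which added that section, 27/08/18. The text of that version still carries both cuts.

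**Criterion 4 does not contradict its own target.** That is correct. Its target concerns delivery as allocated and names no session count. Its bands conflict with the adherence target of criterion 2.

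**Stronger readings that the protocol does not support.**

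- A reader might infer that such a resident fails every criterion. Criteria 1 and 3 count no sessions.
- Section 3.1 says "contingency measures will be implemented if four or more sessions are refused by the resident or missed". Since 12 − 4 = 8, a reader might infer that these measures start only once more than 8 is out of reach. But they include trying again on another day, with the full programme still the aim, so a missed session is not necessarily lost and 8 is not a proven ceiling.
- A reader might infer that the cut defines compliance in the causal models of Section 10.1. That section gives no such definition, and the SAP is not shown.

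**Conclusion.** The point holds as a contradiction in the text as printed: the adherence target includes residents with exactly 8 sessions, while the bands of criteria 2 and 4 and the Section 10.3 proportion exclude them. No other section reconciles the two.

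How much this matters depends on an uptake the protocol does not give. At 75% uptake the reading decides between green and amber in every case tried. At 65% it decides between amber and red unless clustering is strong. At 70% both readings are amber once sessions are clustered, and from 80% upward both are green.

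The effect is confined to the progression recommendation and the descriptive adherence figures. The primary analysis is by intention to treat, so its estimate, power and type I error are untouched. Confidence is moderate, because the printed symbol should first be checked against the original file.

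**What to change.** 1. Check the original protocol file for an underlined greater-than sign in Sections 3.4 and 10.3. If it is there, print an unambiguous at-least sign; the conflict then largely disappears.
2. If it is not, the sponsor should reconcile the criterion 2 target, the bands of criteria 2 and 4, and Section 10.3 to one session count with one operator, before the pilot data are tabulated. Which count is right is the sponsor's decision.
3. Whichever is chosen, give the TSC the proportion with at least 8 and the proportion with at least 9 sessions, so that it can see whether the colour depends on the cut. With real data this needs no model: the two counts differ by the number of residents with exactly 8.

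The cost is a wording change in at most eight places (the target sentence, six bands and Section 10.3) and one extra line in the pilot report. Data collection does not change, since the stimulation diaries and stimulator downloads already record what is needed.

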***Trial continuation decision***

Findings will be reviewed by the TSC and DMEC at 13 months. The trial will continue if the outcomes for all criteria are either green (**continue)** or amber (**continue but modify protocol)** and, if the latter, appropriate strategies can be identified to overcome the issues within an appropriate timeframe.

If the outcome is red **(Discuss discontinuation)**, we will discuss discontinuing with the TSC, DMEC, funder and sponsor. Options may include opening new sites if particular sites are performing poorly on all measures, or intensive re-education and support for the Implementation Support Facilitators.

# 4. TRIAL RECRUITMENT

**4.1 Trial population**

The trial will take place in >20 CHs (nursing or residential) for older adults in England and Scotland. Five hundred men and women resident in CHs who experience UI at least weekly, including those with cognitive impairment, will be recruited.

**4.2 Inclusion and exclusion criteria**

***Inclusion criteria:***

Care home residents:

- with self or staff reported UI of more than once/week
- who use the toilet or toilet aid for bladder evacuation with or without assistance
- who wear absorbent pads to contain UI.

***Exclusion criteria:***

- CH residents with an indwelling urinary catheter
- CH residents with symptomatic UTI
- CH residents with PVRU volume more than 300ml
- CH residents with a cardiac pacemaker
- CH residents with treated epilepsy
- CH residents with bilateral leg ulcers
- CH residents with pelvic cancer
- CH residents on the palliative care register
- Non-English speakers

**4.3 Identifying and approaching participants**

Processes for identifying eligibility and participant recruitment differ in England and Scotland according to relevant legislation on capacity to provide informed consent to participate.

*CH In England - Mental Capacity Act 2005:*

The local PI (senior clinical nurse or manager) in each CH will identify potentially eligible residents and complete a screening log. Study information will be provided to all potentially eligible residents. Where the local PI believes a resident’s capacity is in question, they will identify and provide the information to the resident’s personal consultee (usually a family member or friend). Where a personal consultee is not available a nominated consultee will be identified by the study team, in accordance with the MCA (2005). The local PI will seek agreement from the resident, if they have capacity or personal (or nominated) consultee where relevant, to speak to the RRA to gain information about the study.

*CH in Scotland -Adults with Incapacity (Scotland) Act 2000:*

The local PI (senior clinical nurse or manager) in each CH will identify potentially eligible residents and complete a screening log. Study information will be provided to all potentially eligible residents. Where there is evidence of incapacity (a resident has a certificate of incapacity) the local PI will identify and provide the study information to the resident’s welfare attorney (if one has been appointed) or their nearest relative. If there is no welfare attorney identified, or the resident does not have a relative who can be consulted, they will be considered ineligible to participate in the study. The local PI will seek agreement from the resident, if they have capacity or welfare attorney/nearest relative where relevant, to speak to the RRA to gain information about the study.

**4.4 Informed consent**

Procedures to seek and gain informed consent from eligible potential participants are agreed and confirmed by Research Ethics Committees with responsibility for reviewing applications for research with adults who lack capacity. The application for approval is made via the National Research Ethics Service (two separate submissions – England and Scotland). The research does not involve the NHS; therefore, management approval for CH sites to participate is sought via the individual CH group approval processes.

**Recruitment of residents**

All resident recruitment is undertaken by the RRAs for English and Scottish sites:

*CHs In England - Mental Capacity Act 2005:*

Following confirmation by the local PI of permission to approach the resident (and personal or nominated consultee) the RRA arranges to meet them to provide a full explanation of the study, ensure eligibility and seek consent to participate. Where the resident lacks capacity to consent the consultee provides advice on what they feel the person’s wishes would be if they had capacity. The consultee signs a declaration form if they believe the resident would choose to agree to participate. However, in accordance with the principles of the MCA (2005), ongoing consent (if resident has capacity) or assent is sought from the individual resident at every research contact and before any research activity is undertaken. Consultees may advise at any point that they believe the person’s wishes about participation have changed and they should therefore be withdrawn from study participation.

*CH in Scotland -Adults with Incapacity (Scotland) Act 2000:*

Following confirmation by the local PI of permission to approach the resident or their welfare attorney/nearest relative, the RRA arranges to meet them to provide a full explanation of the study, ensure eligibility and seek written consent to participate. The resident or their welfare attorney/nearest relative signs the consent form. However, in accordance with the principles of the Adults with Incapacity (Scotland) Act (2000) consent is not seen as an all or nothing entity and therefore ongoing verbal consent (if resident has capacity) or assent is sought from the individual resident at every research contact and before any research activity is undertaken. Welfare attorneys or nearest relatives may advise at any point that they withdraw consent for the resident to continue to participate.

**Recruitment of family carers**

Family members of participating residents who lack capacity to consent to participate in an interview are provided with study information by the local PI. Further explanation and the opportunity to ask questions about the study are offered to them by the RRA to enable an informed decision to be made about participation. Written consent to participate in the process evaluation interview is sought from the individual family carer prior to them taking part.

**Recruitment of staff**

Care home staff (RNs, SCs and managers) eligible to participate in the process evaluation will be provided with study information by the local PI. Further explanation and the opportunity to ask questions about the study are offered to them by the RRA to enable an informed decision to be made about participation. Written consent to participate in the process evaluation interviews is sought from the individual staff members prior to them taking part.

**4.5 Randomisation and allocation**

Following consent, baseline data will be collected. Only once all baseline data are recorded will remote randomisation be initiated. Eligible and consenting residents are randomised to one of the two groups (TPTNS or sham) using the proven 24-hour telephone Interactive Voice Response randomisation application or via the web-based application (and phone, if appropriate), both hosted by CHaRT. Information required to perform the randomisation is submitted by the RRA, who has obtained the consent, however to ensure the RRA is blinded to group allocation the information on the allocated group is delivered to the local PI in each CH by the ELECTRIC trial office, who receive the allocation information from CHaRT. The local PI records the allocated group in a separate file and informs the CH staff who will deliver the allocated intervention.

Randomisation will be computer allocated on a one to one basis in random permuted blocks of size two, four or six, with stratification by:

- Sex – male/female
- UI severity - mild (0-200ml/24 hrs); moderate (200-400ml /24 hrs); severe (400+ ml/24 hrs)
- Centre

**4.6 Administration arrangements post recruitment** (if applicable)

Following recruitment, the following administration arrangements will be undertaken:

- The Trial Office will notify the resident’s GP/medical practitioner in writing that the resident has joined the trial.
- The RRA will file a copy of the consent form in the resident’s care notes along with information about the trial.
- The RRA will file a copy of the GP/medical practitioner letter in the resident’s care notes.
- The RRA will enter trial data regarding the resident into the bespoke trial website.
- The RRA will maintain trial documentation at each site in their region (Scotland or England).
- The RRA will return a copy of the signed consent form to the Trial Office in Glasgow.

**4.7 Methods to protect against other sources of bias**

*Attrition*: The major anticipated source of attrition is resident death. Reasons for attrition are accurately recorded in each CH and therefore there should be minimal actual loss of residents to follow up at 18 weeks. Anticipated mortality rates have been accounted for in the sample size calculation and analysis plan.

*Use of sham stimulation as control*: To ensure the resident and their relatives are blind to the allocated intervention group a sham stimulation intervention rather than a no-treatment control is used.

*Contamination:*The risk that residents may receive the alternative intervention to which they were randomised will be addressed by the Implementation Support Facilitator, who will check digital photographs of electrode position taken by delivering nurses/senior carers on a bi-weekly basis and correct any delivery fidelity breach, including checking the stimulation diaries recorded after each session to ensure the information aligns with the allocated group. In addition, the electrical stimulator information downloads will be undertaken bi-weekly and will indicate any delivery protocol breaches, by comparing recorded parameters against the expected.

## 5. OUTCOME MEASURES

#### *5.1 Primary outcome measure*

Volume of UI leaked over a 24-hour period at 6 weeks post randomisation.

#### *5.2 Secondary outcome measures*

*Urinary outcomes*

Volume of UI leaked over a 24-hour period at 12 and 18 weeks post randomisation

Number of pads used in 24 hours at 6, 12 and 18 weeks post randomisation

Patient Perception of Bladder Condition (PPBC)38 at 6, 12 and 18 weeks post randomisation

Family Carer Perception of Bladder Condition (FC-PBC) at 6, 12 and 18 weeks post randomisation

Staff Perception of Bladder Condition (S-PBC) at 6, 12 and 18 weeks post randomisation

Minnesota Toileting Skills Questionnaire (MTSQ)65 at 6, 12 and 18 weeks post randomisation.

*Quality of Life outcomes*

Resident DEMQOL at 6 and 18 weeks post randomisation

Proxy DEMQOL at 6 and 18 weeks post randomisation40

*Economic outcomes*

Resource Use Questionnaire (RUQ) at 6 and 18 weeks post randomisation.

##

